## Abstract

**Background:**

Migraine is one of the most common neurological disorders in clinical practice and is a substantial cause of disability worldwide. Current approaches to therapy are primarily based on medication but are often limited by inadequate effectiveness and common side effects. Newer, more effective medications are expensive. Mindfulness-based stress reduction (MBSR), an 8-week classroom-based meditation intervention, is inexpensive, has no known side effects, and has demonstrated clinically meaningful effectiveness for several chronic-pain syndromes. In addition, MBSR has shown promising results for migraine therapy in a few small case studies and pilot studies. We present here the protocol for a two-arm randomized controlled pilot trial of MBSR for moderate-to-severe episodic migraine, which, if successful, will form the basis for a fully powered clinical trial.

**Methods/design:**

This study, set in Northern California, is a two-arm parallel-comparison single-blinded randomized controlled pilot trial with the goal of recruiting approximately 60 participants with moderate-to-severe episodic migraine. The feasibility outcomes include ability and time required to recruit, adherence to the MBSR treatment, and ability to measure outcomes using 31-day headache diaries and patient-reported questionnaire data. The active treatment arm consists of an 8-week community-based MBSR class plus usual care, and the wait-list control group is usual care. Recruitment is underway and expected to be complete by the end of 2018.

**Discussion:**

To our knowledge, this is the first pragmatic trial in the U.S. of MBSR for migraine using community-based classes, and if it proves viable, we plan to conduct a fully powered trial to determine the effectiveness of the intervention for reducing headache days for moderate-to-severe episodic migraineurs.

**Trial registration:**

Clinicaltrials.gov, NCT02824250. Registered on 6 July 2016.

**Electronic supplementary material:**

The online version of this article (10.1186/s13063-019-3355-y) contains supplementary material, which is available to authorized users.

## Background

Migraine, one of the most common neurological disorders in the U.S., is ranked among the top 20 causes of disability worldwide [1–3]. Migraine is currently one of the leading causes of disease burden for women aged 15–44 years and affects an estimated 11% of the adult population globally, with a strong female predominance [1–4]. The most common approach to therapy is generally focused on pharmaceutical management, which is often limited by insufficient efficacy and frequent side effects. The newest class of migraine-preventive drugs, the calcitonin gene-regulating peptides, while promising, are very expensive and not consistently beneficial for a substantial proportion of the migraine-affected population [5]. Because stress is a common precipitant of migraine episodes, it is rational that a stress-reducing intervention may favorably affect the course of migraine headache [6, 7].

Mindfulness-based stress reduction (MBSR), created in 1979 by Jon Kabat-Zinn at the University of Massachusetts Medical Center, is an 8-week classroom-based intervention that combines mindfulness meditation, yoga, stress psychology and physiology, neuroscience, experiential education, and a group process. Several studies have been published regarding the effects of MBSR on a variety of medical conditions such as chronic pain and mental health [8, 9]. MBSR is inexpensive, can be delivered in a group format, and has no known adverse effects. MBSR has appeared promising in two small case studies and three pilot trials as an effective treatment for moderate-to-severe episodic migraine [10–14]. In particular, one pilot trial of MBSR for patients with episodic migraine found promising outcomes related to the intervention, providing important impetus for future research [11]. Thus, more rigorous and large-scale clinical trials are needed to test the effectiveness of mind-body interventions such as yoga and meditation in improving not only migraine-related pain but mental health outcomes and quality of life for migraineurs. If MBSR is found to be an effective adjunctive therapy for migraine compared to usual care, providers will have an additional safe and inexpensive preventive-treatment option to offer their patients.

We present here the protocol for a two-arm randomized controlled pilot trial of MBSR for patients with moderate-to-severe episodic migraine headaches. The trial is currently in progress. Should this research prove that it is possible to recruit to a trial of community-based MBSR classes and that the treatment is acceptable to participants, the experience gained from this trial will be used to design and implement a fully powered phase III trial with the objective of testing a low-risk intervention to assist patients who suffer from this often debilitating disorder. As this study contains all the elements of a fully powered trial, but with a single site and smaller sample size, it can be classified as a pilot study [15].

This randomized controlled pilot trial (the Mindfulness and Migraine or M&M study) is designed to assess the achievability and acceptability of an 8-week community-based MBSR intervention for patients with moderate-to-severe episodic migraine. The feasibility outcomes include ability and time required to recruit, adherence to the MBSR treatment, and ability to measure outcomes using 31-day headache diaries and patient-reported questionnaire data. Although we are not measuring efficacy, we will collect clinical outcome data to show the feasibility of our data collection methods. The primary clinical outcome is the change from baseline in headache frequency at 4 months derived from headache diaries. Secondary outcomes include change in headache frequency at 8 months post-randomization and other headache-related measures including headache pain, disability, quality of life, and mental health.

## Methods/design

This study is a single-center, parallel, randomized, partially blinded, controlled pilot study (Fig. 1), designed to assess the feasibility of conducting a fully powered effectiveness randomized controlled trial.

**Fig. 1 Fig1:**
[figure not shown]
Study flow diagram. MBSR Mindfulness-based stress reduction

### Setting and participants

#### Clinical sites

All in-person study recruitment and randomization activities take place at the Palo Alto Medical Foundation Research Institute in Northern California. Participants are recruited from three sources: (1) the Palo Alto Medical Foundation, which is a Sutter Health affiliate; (2) Kaiser Permanente Northern California Redwood City Medical Center; and (3) the greater Palo Alto community. Sutter Health is a large not-for-profit integrated health system in Northern California with five health foundations and 24 hospitals serving more than 3 million patients annually. Palo Alto Medical Foundation, the largest of the five medical foundations, is in Palo Alto, California, and serves approximately 1 million patients annually. Kaiser Permanente Northern California is a large integrated health plan with 4.1 million members. Both Sutter and Kaiser use EpicCare® for their electronic health record (EHR) system. Although most patients are initially identified from the EHR in both systems, the workflow for patient recruitment is different for the two entities due to different regulatory requirements (see details below).

#### Eligibility criteria

Participants are adults with moderately severe migraine headaches who meet the eligibility criteria detailed below. A log of potential participants who decline to enter the study or who are deemed ineligible is kept to judge the representativeness of those who consent to be randomized, consistent with CONSORT guidelines [16].

#### Inclusion criteria

Age at least 18 years oldModerate-to-severe migraine headaches, defined as baseline headache frequency of 4–14 headache days per month (over a period of 31 days as determined by the headache diary completed as part of the run-in period)

#### Exclusion criteria

Has practiced MBSR or another meditation technique in the past 6 months (daily prayer is not considered a regular meditation practice)Chronic migraine (i.e., > 14 headache days per month).Cognitively or emotionally impairedPregnantInability to speak or write in EnglishStarted or changed migraine medication (abortive or prophylactic) in the month prior to randomizationIncomplete run-in headache diaryInsufficient availability to attend an approved community-based MBSR class

#### Recruitment

Multiple recruitment strategies were employed for two reasons. First, we recruited from two different health-care systems with different regulatory requirements to maximize the generalizability of our recruitment strategies. Second, different recruitment strategies were used to give a better understanding of the advantages and challenges of the optimal recruiting techniques for this population in preparation for a larger trial.

#### Recruitment at the Sutter Health site

The Sutter institutional review board (IRB) requires active permission from providers for the recruitment of patients into this study. Potentially eligible patients are identified using an EHR-based electronic migraine probability algorithm previously developed and validated by our group [17]. The criteria for active recruitment include a score > 10 from the migraine probability algorithm and an encounter with the site for migraine in the previous 12 months. Providers are given invitation letters for each patient identified and asked to sign those whom they approve. Study personnel then retrieve and mail the signed letters. Each invitation letter contains a return postcard and gives a toll-free number. If patients return the postcard asking to be contacted or they leave a message on the study phone line, the study coordinator calls them for a preliminary screening.

#### Recruitment at the Kaiser Permanente site

Patients with a history of migraine headache are identified from the EHR. The charts of a random sample of these patients are reviewed by the site’s principal investigator to identify those who have clear evidence of migraine and no EHR-identifiable exclusion criteria. The primary-care physicians for these patients are then contacted and, if there are no objections, each patient is mailed a recruitment letter with an opt-out postcard. Those patients who contact the Kaiser study center are called immediately. Those who do not contact the Kaiser study center and have not returned an opt-out postcard are contacted by phone 3 weeks after the letter is mailed. If a patient passes the telephone screen and expresses interest in participating, their contact information is given to the Sutter Health project coordinator, who contacts the patient and arranges an in-person assessment.

#### Community-based recruitment

Several methods are used for community recruitment, including posting flyers at local coffee shops, train stations, and grocery stores. The study is also posted on clinicaltrials.gov (NCT02824250).

### Randomization

Prior to the start of the study, a balanced, blocked randomization list was generated using Stata v14.0 using variable block sizes of 2, 4, and 6 [18]. From the list, a research assistant not affiliated with the study translated the allocation numbers into groups and placed each allocation into an opaque envelope, labeled with a sequential study identifier. The envelopes were then sealed and transferred to the study site.

When each potential participant returns to the clinic with their completed run-in diary (see below), the study staff member verifies their eligibility. If all study eligibility criteria are satisfied, the study staff member opens the next envelope in the sequence and reveals the group assignment to the participant.

### Blinding

Full blinding is not possible for this trial. Study staff who interact closely with patients (e.g., by identifying and scheduling MBSR classes, or performing the randomization) are not blinded. Investigators, statisticians, programmers, and study staff who collect outcome measurements remain blinded to participant treatment assignment until the primary analyses are completed. If a serious adverse event occurs, the study physician (AA) can be unblinded as necessary.

### Study intervention

Participants in the active-treatment group attend a group MBSR class that follows the established protocol for the MBSR intervention as developed by Kabat-Zinn and colleagues at the Center for Mindfulness, University of Massachusetts Medical School [19]. These classes comprise weekly 2.5-h group sessions and a 1-day weekend retreat conducted by a trained MBSR teacher. As this study is designed as a pragmatic trial, participants attend a community-based class for which the instructor and the curricula have been vetted by the study MBSR expert (RS). There are numerous class options for participants within and outside the participating health systems and participants are free to choose any of the approved classes that best matches their availability. The cost of the MBSR classes is covered by study funds. A participant is considered to have successfully adhered to the intervention if they attend at least five of the eight weekly sessions and the 1-day weekend retreat (attendance records are provided by the MBSR instructors). The active treatment is in addition to usual care. The fidelity of the instructor to the vetted curricula was not monitored because of the large number of class options and the potential for such monitoring to become burdensome or intrusive.

Participants randomized to the control arm will continue with their usual activities and complete the study data-collection activities on a schedule identical to that of the MBSR-allocated participants. After the 8-month study period has passed, control-group participants are offered the opportunity to enroll in one of the approved community-based MBSR classes with costs covered by study funds (i.e., a wait-list control).

### Outcome measures

There are two sets of outcome measures for this pilot trial: those relevant to the feasibility objectives (recruitment and intervention adherence) and those relevant to the effectiveness of the MBSR intervention. Explicit criteria for judging the success of the proposed trial methods have been established a priori. Study methods will be deemed successful within each of the following attributes:Recruitment: Enrollment of at least 60 participants within any 36-week period or enrollment of at least 18 participants within any 9-week period.Intervention adherence: At least 80% of intervention-allocated participants completed at least five of the eight weekly MBSR classes and the 1-day weekend retreat.Primary effectiveness outcome: The primary outcome for assessing the clinical effectiveness of the MBSR intervention is the change in frequency of migraine episodes from baseline as measured by a 31-day headache diary at 4 months.Secondary effectiveness outcomes: Secondary measures of intervention effectiveness were selected to capture specific clinical and quality-of-life attributes that may be affected by the MBSR intervention. All secondary outcomes described below are collected and managed using Research Electronic Data Capture (REDCap) tools hosted at Sutter Health [20]. REDCap is a secure, web-based application designed to support data capture for research studies, providing (1) an intuitive interface for validated data entry, (2) audit trails for tracking data manipulation and export procedures, (3) automated export procedures for seamless data downloads to common statistical packages, and (4) procedures for importing data from external sources.Questionnaire Assessments: Questionnaires were chosen to harmonize with the National Institutes of Health (NIH) Patient-reported Outcomes Measurement Information System (PROMIS) measures [21] and the National Institute of Neurological Disorders and Stroke (NINDS) Common Data Elements for Headache Studies [22], supplemented with additional instruments to assess specific domains and for compatibility with prior migraine trials. All instruments are self-administered, and the total respondent burden was kept to less than 30 min. All instruments have undergone psychometric testing and have been found to be acceptable in terms of internal consistency, content validity, concurrent validity, and test–retest reliability. The instruments are summarized in Table 1.

**Table 1 Tab1:** Outcome instruments for the Mindfulness and Migraine Study

Instrument	Domain	Number of items	Time (min)	Source (references)
Migraine Disability Assessment (MIDAS)	Headache	5	2	NINDS [22]
Headache Impact Test (HIT-6)	Headache	6	2	NINDS [22]
Visual analogue scale	Pain	1	1	NINDS [22]
Medical Outcomes Study Short Form 12 (SF-12)	Function	12	4	NINDS [22]
Work Productivity and Activity Impairment (WPAI)	Productivity	6	2	[23]
Migraine-Specific Quality of Life (MSQ)	Quality of life	14	4	NINDS [22]
PROMIS Depression Short Form	Depression	8	3	PROMIS [21]
PROMIS Anxiety Short Form	Anxiety	8	3	PROMIS [21]
Perceived Stress Scale (PSS-10)	Stress	10	3	[25, 26]
Mindful Attention Awareness Scale (MAAS)	Mindfulness	15	5	[27, 28]
Total	–	85	29	–

*NINDS* National Institute of Neurological Disorders and Stroke, *PROMIS* Patient-reported Outcomes Measurement Information System

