### Statistical procedures

#### Sample size

The sample size of approximately 60 participants for this pilot study was determined in collaboration with the funding agency and was felt to be large enough to gauge whether the community-based classes would be feasible for a full-scale clinical trial intervention. This sample will allow us to estimate an adherence rate of 0.8 with confidence limits ±0.1 around the point estimate.

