#### Statistical analysis

As a pilot trial, the feasibility objectives are central and are focused on recruitment, retention, intervention adherence, and data collection. Recruitment rates are calculated as the mean number of participants enrolled into the trial per week divided by the mean number of patients screened per week. In addition, we examine success in meeting the stated recruitment goals described above. Adherence to the intervention is measured dichotomously (as the proportion satisfying the noted adherence definition) and as the distribution of the proportion of all classes completed. Data-collection success rates are estimated by calculating the proportion of all forms fully completed by participants who remain in the trial (i.e., who have not withdrawn), and the proportion of all forms that should have been completed if retention and data collection were 100%. No formal tests of intervention effectiveness are planned, given the intentionally underpowered pilot nature of the study [29, 30].

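### The stated ±0.1 precision for adherence counts all 60 or so participants, but adherence is judged only in the MBSR arm of about 30, where it is about ±0.14

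*Protocol article*

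**What the plan says.** The Outcome measures section of the protocol article announces success criteria fixed in advance: "Explicit criteria for judging the success of the proposed trial methods have been established a priori". They are applied one attribute at a time: "Study methods will be deemed successful within each of the following attributes". For adherence the criterion is "At least 80% of intervention-allocated participants completed at least five of the eight weekly MBSR classes and the 1-day weekend retreat". It is a cut-off on an observed proportion, and its denominator is the MBSR arm.

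The Sample size section reads "The sample size of approximately 60 participants for this pilot study was determined in collaboration with the funding agency", and then gives the only numerical support for that size: "This sample will allow us to estimate an adherence rate of 0.8 with confidence limits ±0.1 around the point estimate". No confidence level is stated.

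The Randomization section describes "a balanced, blocked randomization list was generated using Stata v14.0 using variable block sizes of 2, 4, and 6", and the trial has two arms. The Statistical analysis section adds: "Adherence to the intervention is measured dichotomously (as the proportion satisfying the noted adherence definition"; the distribution of the share of classes completed is reported as well. Under Study intervention, controls are offered a class only once their 8-month study period is over.

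**The concern.** The precision statement and the criterion it supports use different denominators. The precision is attributed to the whole sample, but control participants have no MBSR attendance to measure during the trial, so only about half the sample can inform the adherence estimate.

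This matters because the Statistical analysis section makes feasibility the central aim and plans no formal test of effectiveness. Adherence is one of the two feasibility attributes with an explicit numerical mark; the other is recruitment. A reader who takes ±0.1 at face value would think an observed 80% fixes true adherence more tightly than it does, and would put too much weight on landing just above or just below the mark.

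**Working it through.** **Inputs**
- Adherence rate for the precision statement: 0.8 (Sample size).
- Total sample: about 60 (Sample size).
- Allocation: balanced, two arms (Randomization), so about 60/2 = 30 in the MBSR arm. The 30 is derived; the article does not state it.
- Success mark: observed proportion of at least 80% of the MBSR arm (Outcome measures).
- Confidence level: not stated. 95% is assumed, with 90% and 80% shown.

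**Step 1. Reproduce the stated figure.** Half-width = z × √(0.8 × 0.2 / n).
- n = 60, 95%: 1.96 × √(0.16/60) = 0.101. This matches ±0.1.
- n needed for exactly ±0.1 at 95%: 0.16 × (1.96/0.1)² = 61.5.

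So the stated figure is a 95% limit with everyone in both arms counted.

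**Step 2. Use the denominator of the criterion, n = 30.**
- 95%: 1.96 × √(0.16/30) = 0.143.
- 90%: 1.645 × √(0.16/30) = 0.120.
- 80%: 1.282 × √(0.16/30) = 0.094.

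At 95% the result does not depend on an exact 30: with 26 people it is 1.96 × 0.4/√26 = 0.154, and with 35 it is 1.96 × 0.4/√35 = 0.133.

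**Step 3. Interval at the mark.** 80% of 30 is 24. The Wilson interval for 24/30 has
- centre (0.8 + 1.96²/60) / (1 + 1.96²/30) = 0.864/1.128 = 0.766;
- half-width 1.96 × √(0.16/30 + 1.96²/3600) / 1.128 = 0.139;
- limits 0.63 to 0.90.

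The exact (Clopper–Pearson) interval is 0.61 to 0.92.

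**Step 4. How the criterion behaves with 30 people.** P(met) = P(X ≥ 24), with X binomial(30, p).

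| True adherence | Criterion met | Criterion missed |
|---|---|---|
| 0.60 | 0.017 | 0.983 |
| 0.70 | 0.160 | 0.840 |
| 0.75 | 0.348 | 0.652 |
| 0.80 | 0.607 | 0.393 |
| 0.85 | 0.847 | 0.153 |
| 0.90 | 0.974 | 0.026 |

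Because 80% must be rounded up to a whole count, the chance of a miss at a true 0.80 moves with the realised arm size. Over 26 to 35 people it runs from 0.39 (n = 30, 24 needed) to 0.54 (n = 29, 24 needed), so 39% is the low end.

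**The case against.** A reader might infer something stronger: that the pilot fails two times in five when adherence is exactly as planned, so that a workable intervention would be rejected. The documents do not support this, for three reasons.
- Success is judged attribute by attribute. No overall pass or fail rule is given, and nothing says that missing one mark stops the full trial. The Discussion speaks of carrying lessons into later designs. What can be missed is the adherence criterion, not the pilot.
- The article never calls 0.8 the expected rate. It is the value at which precision is quoted, and it coincides with the success mark. If 80% is a minimum and higher adherence is expected, the criterion separates good from poor adherence reasonably well for a pilot: missed 3% of the time at 0.90, met 2% of the time at 0.60.
- Missing a cut-off roughly half the time when the truth sits on it is a property of any cut-off. With all 60 counted and 48 needed, the miss probability at 0.80 would still be 42%.

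All of this stands. None of it repairs the precision statement.

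A narrower defence is that no confidence level is given, and at 80% confidence 30 people do give ±0.09. That is possible, but 80% limits would be unusual without saying so, while the 95% calculation on 60 people gives 0.101. The mismatch in denominator is much the likelier explanation.

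Finally, the full protocol or the SAP may specify how the interval is to be reported. That may be so, and the absence of a reporting rule is not the point here. The point is a figure that the article does print.

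**Conclusion.** The concern holds for the precision statement. The ±0.1 corresponds to 95% limits on about 60 people, whereas the adherence estimate comes from about 30 and has limits of about ±0.14. The understatement is a factor of about √2 (0.143/0.101 = 1.41). The evidence behind the 80% criterion is correspondingly weaker than the article suggests, in both directions: at a true 0.70 it is met 16% of the time, and at a true 0.85 it is missed 15% of the time.

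This rests on equal arms of about 30, on 95% confidence and on independent participants. At 90% confidence the half-width is ±0.12, so the conclusion is unchanged; only a level near 80% would rescue the stated figure.

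A reader might go on to infer that the 80% rule itself needs replacing, for example by adding an intermediate zone. That does not follow. With the mark kept at 24 of 30, it would still be missed 39% of the time at a true 0.80, and 24 of 30 would still pass. A softer zone would also loosen a criterion set in advance, after recruitment had closed (Trial status: 21 September 2018).

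**What to change.** 1. In Sample size, replace the ±0.1 by about ±0.14, state that it is a 95% limit, and say that it refers to the roughly 30 participants allocated to MBSR.
2. When adherence is reported, give the observed proportion in the MBSR arm with its 95% Wilson interval, using the realised arm size, beside the 80% criterion. Leave the criterion itself unchanged.

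Neither step alters the design, the data collected or the prespecified success mark. The cost is a less favourable stated precision.
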